#### Secondary outcomes/study parameters

o*Clinical outcomes:*Need for operation which is evaluated between 10 and 14 days post burn. Reasons for operation are that the experienced burn specialist expects no further wound healing in the next 7 to 11 days of the partial thickness area or a full thickness burn. If the decision to graft is made before 10 to 14 days post burn then the operation will still performed before 10^th^ day post burn day. The only indication for operation before the 10^th^ PBD is when a partial thickness burn becomes a full partial thickness burn. The treatment of full thickness burns is split skin graft in an early stagePercentage TBSA of the study area that covered with skin graftColonization: twice a week a wound swab will be taken from the study area. The wound swab will then be sent for laboratory investigation. In brief, the analysis of the wound swab will include the following steps. The microscopic examination will entail gram-staining. Thereafter, a quantity of the specimen will be cultured to obtain a pure single specimen culture. Finally, the sensitivity of the organisms to specific local therapy will be determined. In case of wound colonization the treatment will be changed to another relevant treatment based on the results of the wound cultureInfection: infection is suspected if a combination of skin redness, pain, swelling, tenderness, warmth, fever or pus draining from the wound is present. Infection is a clinical evaluation of the wound, in presence of absence of positive wound culture, and is judged by a physician at the burn center during each dressing changeNumber of dressing changesUse of systemic antibioticso*Patient-reported outcomes:*Pain will be measured during the application and removal of the wound dressing (procedural pain, measured directly after dressing change) and background pain (measured in the morning and evening). Pain will be measured twice daily during hospital admission by use of a Visual Analogue Thermometer (VAT), which is a numeric scale from 0 (no pain) to 10 (worst imaginable pain)Itching will be measured daily in the evening during hospital admission by use of a VAT [31]Anxiety: the Burn Specific Pain Anxiety Scale (BSPAS) will be scored on day 7 ± 2 post burn and on the day of discharge. The BSPAS is a valid and reliable nine-item self-report scale for the assessment of pain-related and anticipatory anxiety in burned patients [32, 33]Health-related quality of life (HRQoL) will be measured using the following questionnaires, in the week before discharge and at 3, 6 and 12 months post burn:Burn-specific quality of life (QoL) will be measured using the Dutch version of the Burn Specific Health Scale (BSHS)–Brief [34, 35]. The BSHS-Brief is a valid and reliable self-administered questionnaire that covers nine domains (heat sensitivity, affect, hand function, treatment regimens, work, sexuality, interpersonal relationships, simple abilities, and body image). The questionnaire takes 10–15 minutes to complete and 5 minutes to score. Responses are scored by the patient on a five-point scale from 0 (extreme) to 4 (none/not at all) for each of the 40 items. Mean scores are calculated for each of the domainsGeneral HRQoL will be measured using the EuroQol-5D (EQ-5D) questionnaire [36]. This simple and generic description of health status is widely used in studies on clinical and economic appraisal. The EQ-5D outcomes will be converted in utility scores between 0 (death) and 1 (perfect health) based on empirical valuations [37]. From the area under the utility curve during the 12 months of follow-up quality- adjusted life years (QALYs) will be calculatedo*Scar formation*: the following aspects of scar formation will be measured after 3, 6 and 12 months post burn:Scarring will be measured using the Patient and Observer Scar Assessment Score (POSAS), a valid and reliable scale that is designed for the evaluation of all types of scars by professionals and patients. It consists of two numeric scales: the Patient Scar Assessment Scale which is completed by the patient and the Observer Scar Assessment Scale which is completed by the medical staff. The variables scored by the patient are pain, itching, color, stiffness, thickness and irregularity [38–40]. The variables scored by the medical staff include vascularization, pigmentation, thickness, relief and pliabilityElasticity will be measured using a Cutometer (Courage & Khazak, Köln, Germany), a validated instrument to measure the vertical deformation of the skin in millimetres when the skin is pulled by means of a controlled vacuum into a circular aperture [41]Scar color and pigmentation will be measured using the DSM II colorimeter (Dermaspectrometer).This is a validated instrument to measure scar color by a narrow-band simple reflectance meter [41]o*Total (medical and non-medical) costs:* total costs in this study represent direct health care costs (inpatient and outpatient medical costs), direct non-healthcare costs and indirect non-health care costs (productivity loss). Personnel time and used materials for wound care and surgical procedures, hospital days for initial stay and re-admittance and outpatient visits during the first year will be measured prospectively as part of the case record form. Health resource use outside the hospital, travel costs and productivity losses will be recorded by questionnaires filled out by the patients at 3, 6 and 12 months post burn. Cost of dressing changes and surgical procedures will be assessed by translating the personnel time and used materials into costs by means of gross salaries and market prices. The costs of hospital stay and outpatient care in burn centers will be calculated by multiplying the number of hospital days respectively outpatient visits with their cost prices [42]. Other healthcare use will be translated into costs by standard prices [43]. Productivity losses will be valued using the friction cost method [44]o*Baseline parameters:* age, gender, skin type, wound etiology, bacterial contamination at admission, location of the wound, type of wound, TBSA% and co-morbidities. In all patients, the burn depth of the study area will be accurately determined on day 2–5 post burn by clinical evaluation and LDI scan using the moorLDI2-Burn Imager™ (Moor Instruments, Axminster, UK) and, based on pre-defined criteria (Table 1), be classified as superficial, intermediate or deep partial thickness injury. The size of each burn wound is then estimated in TBSA. In a LDI the low-intensity laser beam is scanned across a tissue surface in a raster fashion using a moving mirror. There is no direct contact with the tissue being assessed. The wounds are scanned by a trained research physician or nurse, after removal of topical medication (during regular wound treatment). All research physicians and nurses in both burn centers have followed the same training sessions and have the same experience. The scanning will take 1–5 minutes.

**Table 1 Tab1:** Clinical assessment and laser Doppler imaging (LDI) results

Classification	Clinical properties						LDI color
	Blisters	Color/Appearance	Pliability	Capillary refill	Pain	Healing time	
Superficial partial thickness burns	Small blister: intact and open	Pink-red, shiny	Supple	<2 sec	++	Within 14 days	Red
Intermediate partial thickness burns	Blisters: intact and open	Pink-red, shiny and dry	Mix of supple and stiff	<2 sec	+	14–21 days	Yellow
Deep partial thickness burns	Blisters: intact and open	Red, shiny and dry	Mix of supple and stiff	>2 sec	+/-	>21 days or even no spontaneous healing	Blue
Full thickness burns	None	White-yellow, red, brown and black	Stiff	>2 sec	-	No spontaneous healing	Blue

A schedule with baseline and outcome measurements during the study is presented in Table 2.

**Table 2 Tab2:** Time schedule for study procedures and assessments

Procedure/Assessment	Admission	Treatment phase	Follow-up (month)		
			3	6	12
Standard screening, baseline procedures	x				
Check eligibility (inclusion criteria)	x				
Provide patient Information	x				
Obtain written informed consent	x	x (confirmation by patients who were initially non-competent)			
Randomization (Flaminal® vs Flamazine®)	x				
Baseline parameters	x				
LDI		x			
Wound colonization	x	x			
Wound healing		At each dressing change			
Need for surgery of partial and/or full thickness burns and % of study area requiring skin graft		10–14 PBD			
Colonization	x	Swabs on Mondays and Thursdays			
Infection	x	Clinical judgment during dressing changes			
Dressing changes	x				
Use of systemic antibiotics	x				
Pain and anxiety					
Visual analogue thermometer (VAT)	x	Daily, before and after dressing change and in the evening			
Itching	x	Daily in the evening on 7^th^ ±2 PBD and day of discharge			
Burn Specific Pain and Anxiety Score (BSPAS)	x				
Health-related quality of life (HRQoL)		In the last week of hospitalization			
Burn Specific Health Scale Brief (BSHS-Brief)		In the last week of hospitalization	x	x	x
EuroQol-5D (EQ-5D)			x	x	x
Scarring					
POSAS			x	x	x
Cutometry			x	x	x
Dermaspectrometry			x	x	x
Costs		Daily	x	x	x

*LDI* laser Doppler imaging, *PBD* post-burn day

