### Objectives

The aim of this study is to evaluate the clinical effectiveness, quality of life and cost-effectiveness of Flaminal**®** versus Flamazine**®** (SSD) in the treatment of partial thickness burns.

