### Statistical analysis

The analysis will be performed according to the intention-to-treat principle. The baseline patient characteristics will be described as mean ± standard deviation for normally distributed continuous variables, as median (range) for skewed continuous variables, and as number (proportion) for categorical variables. Differences in time to complete re-epithelialization will be compared in both treatment groups will be analyzed with Kaplan-Meier curves and log rank test.

If the baseline characteristics seem unbalanced despite randomization, a multivariable Cox regression analysis will be performed to correct for potentially confounding variables to confirm the primary analysis.

The secondary clinical and patient-reported outcomes on specific follow-up moments will be compared between the treatment groups using the two-sided *t* test or Mann-Whitney test for continuous data, and a two-sided Chi-square test or Fisher’s exact test for categorical data. Repeatedly measured study parameters such as pain and quality of life will be also analyzed using a linear mixed model with treatment as fixed effect and patient as random effect. In the analyses, *p* values <0.05 will be considered statistically significant.

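### The quality-of-life comparison names no covariates, although age and burn size are recorded at entry; this gives up some precision but does not bias the result.

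*Protocol article*

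**What the plan says.** All references are to the protocol article.

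- **Aim.** The Objectives section sets out to evaluate the "clinical effectiveness, quality of life and cost-effectiveness of" the two treatments.
- **Timing.** Under Secondary outcomes, quality of life "will be measured using the following questionnaires, in the week before discharge and at 3, 6 and 12 months post burn"; the questionnaires are BSHS-Brief and EQ-5D. In Table 2 neither questionnaire has a mark at admission; the earliest entry in the quality-of-life block is "In the last week of hospitalization". Every score therefore follows randomization and the start of open-label treatment.
- **Analysis of quality of life.** The Statistical analysis section plans a two-sided *t* "test or Mann-Whitney test for continuous data" at specific follow-up moments. Repeated measures, with quality of life given as an example, are also analysed by a "linear mixed model with treatment as fixed effect and patient as random effect". No patient covariate is named.
- **Adjustment elsewhere.** If baseline characteristics appear unbalanced, "a multivariable Cox regression analysis will be performed to correct for potentially confounding variables to confirm the primary analysis". No adjustment is described for any other outcome.
- **What is known at entry.** The baseline parameters are "age, gender, skin type, wound etiology, bacterial contamination at admission, location of the wound, type of wound, TBSA% and co-morbidities", and Table 2 places them at admission. Age and TBSA% also decide eligibility (Study population).
- **Allocation.** Randomization is 1:1 and stratified by center (Recruitment, consent and randomization).

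**The concern.** The trial admits adults with no upper age limit and burns of up to 30% TBSA, with at least 1% TBSA of partial thickness burn. Both age and burn extent may plausibly explain part of the variation in BSHS-Brief and EQ-5D during the year after the burn. In an unadjusted comparison that variation stays in the error term.

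The scores have no pre-treatment counterpart, so entry characteristics are the only pre-randomization information available to reduce the error variance. The trial is sized on healing time alone, with 41 evaluable patients per arm, and claims no power for quality of life. At stake are wider intervals than necessary for a stated aim. There is also the risk that, with nothing prespecified, any later adjustment would be chosen after the data are seen.

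**Working it through.** **1. The plan's own sample size.** Inputs from Sample size calculation: difference 11 − 6 = 5 days, SD 7.5, alpha 5% (taken as two-sided), power 80%.

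n per arm = 2 × (1.96 + 0.84)² × 7.5² / 5² = 35.3, rounded up to 36. The exact *t* test gives 37. The stated figure is 41, at which power is about 85%. The stated number is therefore conservative for healing time. It has no bearing on this point except that 41 per arm is the number available for quality of life.

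**2. Inputs for quality of life.** n = 41 per arm comes from the document. R2, the share of score variance explained by age and TBSA%, is not given and is assumed at 0.05 to 0.30. A true difference of 0.5 SD is also an assumption, used only for illustration.

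**3. Formulas**, for one visit, in SD units:

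- Unadjusted standard error: sqrt(2/41) = 0.22 SD.
- Adjusted standard error: 0.22 × sqrt(1 − R2).
- Equivalent number per arm: 41 / (1 − R2).
- Difference detectable with 80% power: 0.626 × sqrt(1 − R2), where 0.626 is the exact *t*-test value at 41 per arm.
- Power at 0.5 SD (normal approximation): Φ(0.5 / [sqrt(2/41) × sqrt(1 − R2)] − 1.96).

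| Assumed R2 | Standard error ratio | Equivalent n per arm | Detectable difference | Power at 0.5 SD |
|---|---|---|---|---|
| 0 (unadjusted) | 1.000 | 41 | 0.63 SD | 62% |
| 0.05 | 0.975 | 43 | 0.61 SD | 64% |
| 0.10 | 0.949 | 46 | 0.59 SD | 67% |
| 0.20 | 0.894 | 51 | 0.56 SD | 72% |
| 0.30 | 0.837 | 59 | 0.52 SD | 77% |

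The exact *t* distribution gives powers about one point lower: 61% unadjusted, and 66%, 71% and 76% at R2 of 0.1, 0.2 and 0.3. The gain in effective numbers is 1/0.95 = 1.05 to 1/0.70 = 1.43, that is 5% to 43%.

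**4. Cost in degrees of freedom.** Two covariates multiply the standard error by about sqrt(80/78) = 1.013. Net of this, the ratios at R2 of 0.05, 0.10, 0.20 and 0.30 become 0.987, 0.961, 0.906 and 0.847. The break-even is R2 = 2/80 = 0.025. Adding center as a third term gives sqrt(80/77) = 1.019, before any variance that center itself explains.

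**5. Chance imbalance.** A typical difference between arms in one covariate is sqrt(2/41) = 0.22 SD. At R2 = 0.2 it moves the outcome difference by 0.22 × sqrt(0.2) = 0.10 SD. In variance terms, 0.2 × (2/41) = 0.0098 out of 2/41 = 0.0488. This is one fifth of the variance already inside the unadjusted standard error.

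**The case against.** **The article is a condensed account.** The sentence on the mixed model also omits visit and center, so it may be shorthand, and covariates for secondary models are often left to the analysis plan. This lowers the weight of the point. It does not remove it: the section does take up adjustment, provides it for the primary outcome only, and names unadjusted tests and a fixed effect for the rest. The recommendation stands as a better choice than the one stated.

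**The missing pre-treatment score.** A reader might infer that the absence of a baseline questionnaire is itself a fault. The document does not support that. BSHS-Brief is burn-specific, so no pre-burn value exists, and patients enter acutely, some sedated or intubated. A recalled pre-burn EQ-5D could in principle have been collected, but the Trial status section says recruitment closed on 20 October 2015.

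**Bias.** A reader might also infer that imbalance in age or burn size biases the comparison, or adds an error on top of the wide interval. It does neither. Under randomization the unadjusted difference is unbiased, and step 5 shows that the 0.10 SD shift is already counted in its standard error.

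**The size is assumed.** This stands in full. Neither R2 nor a 0.5 SD difference is in the document, and the eligibility limits say nothing about how age and TBSA% are distributed among those enrolled. The power figures are for one visit and ignore the repeated-measures model.

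**Conclusion.** The point holds as a loss of precision on a secondary outcome that is also a stated aim. The plan names no adjustment for quality of life, while two plausible predictors are on file before randomization. For an assumed R2 of 0.05 to 0.30 the interval would narrow by about 3% to 16% before the cost in degrees of freedom, and by about 1% to 15% after it for the two covariates. Near R2 = 0 there is no gain and a loss of about 1%. The possible benefit is thus much larger than the possible cost, but its true size is unknown.

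The conclusion rests on age and TBSA% being related to the scores, which the document makes plausible but does not quantify. Neither the validity of the quality-of-life comparison nor the primary conclusion is in question.

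**What to change.** Before the quality-of-life data are analysed, amend the Statistical analysis section or the analysis plan as follows:

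- Include admission TBSA%, age and center (the stratification factor) as fixed effects in the planned linear mixed model for BSHS-Brief domains and EQ-5D, whatever imbalance is observed.
- Give the model visit and treatment-by-visit terms, so that it yields a treatment difference at each of 3, 6 and 12 months. Make these the main reported comparison, with the unadjusted tests as supportive.
- Use the TBSA% recorded at admission. The size estimate made with the depth assessment on days 2–5 may come after treatment has begun.
- Do not enter the discharge-week score as a baseline covariate. It is measured after treatment starts and may already reflect it.

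The cost is three model terms and a short amendment, with no new data. By step 4 that is at worst about 1% to 2% in standard error. Data collection was planned to run to November 2016, so the change was still open when the article was published.

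### Cutometer and colorimeter scar readings are compared between different patients with no stated adjustment for skin type, wound location or age, although all three are recorded at baseline; the cost is precision, not validity

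*Protocol article*

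**What the plan says.** Under Secondary outcomes/study parameters, scar formation has its own heading: "the following aspects of scar formation will be measured after 3, 6 and 12 months post burn". Two instruments are used. For colour, "Scar color and pigmentation will be measured using the DSM II colorimeter (Dermaspectrometer"). For elasticity, the Cutometer is described as "a validated instrument to measure the vertical deformation of the skin in millimetres". Table 2 schedules both only at the three follow-up visits.

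The same section lists the baseline parameters: "age, gender, skin type, wound etiology, bacterial contamination at admission, location of the wound, type of wound, TBSA% and co-morbidities".

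Under Statistical analysis, secondary clinical and patient-reported outcomes "will be compared between the treatment groups using the two-sided *t* test or Mann-Whitney test for continuous data". Repeatedly measured parameters, with pain and quality of life as examples, are also analysed by a "linear mixed model with treatment as fixed effect and patient as random effect". Covariates appear once: if baseline looks unbalanced, "a multivariable Cox regression analysis will be performed to correct for potentially confounding variables to confirm the primary analysis".

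Under Recruitment, consent and randomization, allocation is 1:1 and stratified by center only, and all of a patient's burns receive the allocated treatment.

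**The concern.** A pigmentation reading reflects the patient's own skin colour as well as the scar, and skin type is itself a classification of pigmentation. It is a plausible assumption, not a statement of the documents, that skin deformation in millimetres also varies with age and body site. Each patient receives one treatment, so the comparison is between people, and the eligibility criteria restrict neither skin type nor body site. There is no pre-injury reading to adjust for.

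Variation between people that has nothing to do with treatment therefore stays in the error term of the only two instrument-based scar measures. In a trial with about 41 patients per arm, a chance difference in skin type or wound site between the arms would also move the observed scar difference. The variables that could deal with both are already collected, yet no stated scar analysis uses them.

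**Working it through.** **Inputs.** From Sample size calculation: 41 per arm, 82 in total, after 10% attrition from 90. That figure was derived for healing time. No sample size, SD or detectable difference is stated for the scar readings, so there is no plan figure to reproduce on this point; 41 serves only as the number likely to be analysed. The share of variance in a reading explained by the covariates (R²) is not given. *Assumption:* 0.1 to 0.5.

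**1. What is detectable without adjustment.** At one visit, two-sided 5%, 80% power: (1.96 + 0.84) × √(2/41) = 2.80 × 0.221 = 0.62 SD.

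**2. Gain from adjustment, net of its cost.** Adjustment multiplies the variance by (1 − R²), but estimating p covariate terms inflates it on average by 1 + p/(n − p − 3).

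- Five terms, for example center 1, age 1, skin type in two groups 1, location in three groups 2: 1 + 5/74 = 1.068.
- Ten terms, for example center 1, age 1, six skin types 5, four site groups 3: 1 + 10/69 = 1.145.

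| Assumed R² | SE factor, five terms | SE change, five terms | Detectable difference, five terms | SE change, ten terms |
|---|---|---|---|---|
| 0.1 | √(0.9 × 1.068) = 0.980 | −2% | 0.61 SD | +1.5% |
| 0.2 | √(0.8 × 1.068) = 0.924 | −8% | 0.57 SD | −4% |
| 0.5 | √(0.5 × 1.068) = 0.731 | −27% | 0.45 SD | −24% |

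With five terms the break-even is R² = 1 − 1/1.068, about 0.06.

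**3. Chance imbalance.** The difference between arms in a standardized covariate has standard error √(2/41) = 0.221, with a 95% range of ±0.43 SD. An imbalance of k standard errors shifts the unadjusted scar difference by k × √R² × 0.221 SD.

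| Assumed R² | Shift at 1 SE | Shift at 1.96 SE | Error rate given a 1.96-SE imbalance |
|---|---|---|---|
| 0.1 | 0.07 SD | 0.14 SD | 8% |
| 0.2 | 0.10 SD | 0.19 SD | 11% |
| 0.5 | 0.16 SD | 0.31 SD | 21% |

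The last column is 1 − Φ((1.96 − k√R²)/√(1 − R²)) + Φ((−1.96 − k√R²)/√(1 − R²)) at k = 1.96. With no imbalance (k = 0) the same formula gives 3.9%, 2.8% and 0.6%.

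**4. Overall error rate.** In 20,000 simulated trials with 41 per arm and a true null, the unadjusted t test rejected in 5.01% at R² = 0.3 and in 5.01% at R² = 0.5. The conditional excesses and deficits average out.

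**The case against.** Unadjusted comparison of secondary outcomes in a randomized trial is valid and common, and fuller covariate specification is often left to an analysis plan, which is not shown. This stands as to validity, and it limits the weight of the point. It does not remove it: the article names the tests and ties adjustment to the primary endpoint.

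A reader might infer that the readings are analysed as raw scar values with no healthy-skin reference. The documents do not say so. They are silent on a reference site, and a condensed article may leave probe placement and derived scores to the full protocol. Describing the Cutometer as measuring in millimetres tells us about the device, not necessarily about the analysed variable. If reference skin is read and used, part of the problem is already handled.

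A reader might also infer that chance imbalance produces false findings of better or worse scarring. Across randomizations it does not: the level stays at 5%, because the standard error already allows for imbalance.

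It is not explicit that the scar readings fall under the sentence on secondary clinical and patient-reported outcomes, since scar formation has its own heading. Nor is it explicit that they count as repeatedly measured parameters. On either reading no covariate is named; if neither applies, the article states no scar analysis at all.

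Finally, the gain rests on an assumed R², and a model with many terms can lose precision, as the ten-term column shows. That is correct and shapes the fix. Colour, pigmentation and pliability are also scored on the POSAS, so conclusions on scarring do not rest on the devices alone.

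**Conclusion.** The point holds as a matter of precision and of conditional imbalance. No analysis stated for the scar readings uses skin type, wound location or age, and the only provision for adjustment concerns healing time. The planned tests are not invalid or systematically biased.

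The size is uncertain because the documents give no R². Under the assumed range of 0.1 to 0.5, with about five covariate terms and 82 patients, the standard error would fall by about 2% to 27%. At R² = 0.1 the gain is negligible; at 0.5 the detectable difference at one visit falls from 0.62 to 0.45 SD. These figures assume that 41 per arm are measured and that the covariate effects are roughly linear and additive. The outcomes are secondary, so neither the primary conclusion nor the sample size is touched.

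**What to change.** Before the scar data are analysed, state that the Cutometer and DSM II readings at 3, 6 and 12 months will be analysed by a linear mixed model. Fixed effects: treatment, visit, center, age, coarsely grouped skin type and coarsely grouped wound location. Random effect: patient. This replaces the unadjusted tests for these readings. Fix the groupings in advance and keep the covariates to about five terms.

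State also whether the patient's own healthy skin is measured. If the full protocol takes that reading, use it as a covariate or analyse the scar-minus-healthy difference in the same model. Make clear in Statistical analysis that the scar readings are covered.

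The cost is a change of analysis wording and a few degrees of freedom, with little or no gain if the covariates explain 10% of the variance or less. No new data are needed, since the covariates are listed as baseline parameters. Timing matters: Trial status gives recruitment as complete and data collection as planned to end in November 2016, and in an open-label trial covariates chosen after the results are seen would carry little weight.

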### Interventions

The patient will be allocated to one of the following treatments:o*Flaminal® Forte:* treatment with Flaminal® Forte (glucose oxidase-lactoperoxidase guaiacol complex of 50 g in 5.5 % alginogel) will be initiated within 24 hours after admission. Before applying Flaminal® Forte on the wound, pain medication must be given. Paracetamol, Oxynorm and Oxycontin will be used as standard pain medication. The usage and doses of pain medication will be monitored. The burn wound will be cleaned and rinsed with Prontosan® followed by careful dabbing and drying of the wound. The wound will then be covered with a non-adhesive dressing on which a sufficiently thick layer (4–5 mm) of Flaminal® Forte has been applied. A net bandage/dressing will be used to keep the dressing in place. Dressing changes will be performed daily during the first 3 days post burn and thereafter every other day. If an infection is suspected, or in case of leaking or insufficient gel, the dressing with Flaminal® Forte may be changed daily after 3 days post burn. In case of wound colonization or infection, treatment with Flaminal® Forte will be changed to another relevant treatment based on the results of the wound cultureo*Flamazine®:* treatment with Flamazine® (silver sulfadiazine 10 mg/g in hydrophilic crème base) will consist of daily washing and application of Flamazine®. Before applying Flamazine® on the wound, pain medication must be given. Paracetamol, Oxynorm and Oxycontin will be used as standard pain medication. The usage and doses of pain medication will be monitored. The burn wound will be cleaned and rinsed with Prontosan® followed by carefully dabbing and drying of the wound. A sufficiently thick layer (at least 2–3 mm) of Flamazine® will be applied directly on the wound. The cream will be covered with a non-adhesive dressing. A net bandage/dressing will be used to keep the dressing in place. This procedure is repeated once every 24 hours until the sixth day post burn. Thereafter, the treatment of all patients in this study arm will consist of Furacine Soluble Dressing (Furacine 2 mg/g ointment) on the seventh day post urn, and Flamazine® on the eighth day post burn. Treatment with Furacine Soluble Dressing and Flamazine® will be alternated until complete wound healing/operation because of the cytotoxicity of the silver particles in Flamazine® on the wound bed when used continuously. In case of wound colonization or infection the treatment will be replaced with another relevant treatment based on the results of the wound culture

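### Infection is judged at dressing changes whose frequency depends on the arm (14 v 8 scheduled looks by day 14), which tends to give more patients called infected with Flamazine at equal true risk

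*Protocol article*

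**What the plan says.** Infection is a listed secondary outcome. Besides an admission assessment, Table 2 times it as "Clinical judgment during dressing changes". The Secondary outcomes section agrees: it is "judged by a physician at the burn center during each dressing" change. The criterion is clinical: "infection is suspected if a combination of skin redness, pain, swelling, tenderness, warmth, fever or pus draining from the wound is present". No number of signs is set. A culture is not required: "Infection is a clinical evaluation of the wound, in presence of absence of positive wound culture". The section on recruitment and randomization says that outcome assessment cannot be blinded.

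The dressing calendar differs by arm (Interventions). For Flaminal Forte: "Dressing changes will be performed daily during the first 3 days post burn and thereafter every other day". An exception applies: "If an infection is suspected, or in case of leaking or insufficient gel, the dressing with Flaminal® Forte may be changed daily" after that point. For Flamazine: "This procedure is repeated once every 24 hours until the sixth day post burn". From day 7 that arm alternates two products on successive days, so changes stay daily.

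Under Statistical analysis, categorical secondary outcomes are compared by a two-sided chi-square or Fisher's exact test. The number of assessments is not mentioned.

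**The concern.** Treatment allocation sets how often a patient is examined for infection. The signs are non-specific: Table 1 itself lists pain and pink-red or red color among the ordinary features of partial thickness burns. Each look therefore carries some chance of a false-positive call, and the arm with more looks collects more of them.

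The Background presents as unsettled both whether silver prevents wound infection and how bacteria grow under Flaminal. An apparent infection advantage for Flaminal that came partly from the dressing calendar would mislead on a question the trial is meant to inform.

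**Working it through.** **Scheduled looks.** Count from post-burn day 1, using the two regimens under Interventions. Flamazine: every day. Flaminal: days 1, 2, 3, 5, 7, 9, 11, 13 and so on.

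| By day | Flamazine | Flaminal |
|---|---|---|
| 7 | 7 | 5 |
| 14 | 14 | 8 |
| 21 | 21 | 12 |

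Starting the count on day 0, 2 or 3 gives 15 v 9, 13 v 7 or 12 v 6 by day 14, so the gap stays at 6. The plan states no number of looks, so it has no figure to reproduce.

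**Assumptions.** There is no true infection in either arm. The false-positive chance per look, p, is 1, 2 or 3%; this is assumed, since the documents give no rate. There are 45 patients per arm (90 randomized 1:1). Rejection rates come from exact enumeration of the two binomial counts, two-sided at 5%.

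**Independent looks.** P(at least one false positive) = 1 − (1 − p)^k, with k = 14 or 8. For p = 1%: 1 − 0.99^14 = 13.1% and 1 − 0.99^8 = 7.7%.

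**Signs that persist.** Let the daily false sign have prevalence p and day-to-day correlation ρ. After a negative look, the chance of a positive look g days later is p(1 − ρ^g). So P(at least one) = 1 − (1 − p) × the product over successive looks of [1 − p(1 − ρ^g)]. By day 14 Flamazine has 13 gaps of one day; Flaminal has two gaps of one day and five of two days. Mean sign duration is 1/[(1 − p)(1 − ρ)], about 2 days at ρ = 0.5. For p = 2%, ρ = 0.5:

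- Flamazine: 1 − 0.98 × 0.99^13 = 14.0%
- Flaminal: 1 − 0.98 × 0.99^2 × 0.985^5 = 10.9%

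**Results by day 14.**

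| | p = 1% | p = 2% | p = 3% |
|---|---|---|---|
| Independent: Flamazine v Flaminal | 13.1% v 7.7% | 24.6% v 14.9% | 34.7% v 21.6% |
| – chi-square rejects | 14.6% | 22.1% | 29.1% |
| – Fisher rejects | 7.0% | 14.0% | 20.9% |
| About 2 days (ρ = 0.5) | 7.3% v 5.6% | 14.0% v 10.9% | 20.3% v 16.0% |
| ρ = 0.9 | 2.3% v 2.1% | 4.5% v 4.2% | 6.7% v 6.3% |

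The ratio of patients called infected is 1.6–1.7 with independent looks, about 1.3 at ρ = 0.5 and 1.07 at ρ = 0.9. At ρ = 0.5, rejection is about 7–9% by chi-square and 1–5% by Fisher.

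**Same looks in both arms.** With eight common looks and independence, both arms have 7.7, 14.9 or 21.6%, and chi-square rejects in 5.4–6.0% of trials.

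**The case against.** Several objections stand, and they limit the size rather than the direction.

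- **Independence is the extreme case.** Redness, swelling or warmth seen one day may well be there the next. A reader might infer that the schedule makes 15–29% of trials falsely significant. The documents do not support that: it requires independent daily looks, the chi-square test and a full 14 days on schedule, all together. The plan also allows Fisher's test, whose rejection rate is lower throughout.
- **Not every patient has 14 v 8 looks.** Healing, operation, a culture-driven change of treatment or discharge to local outpatient care ends the schedule. By day 7 the looks are 7 v 5 and, even with independence, chi-square rejection is 7.2, 9.2 or 10.4% for p = 1, 2 or 3%. The sample size section expects mean healing at 11 v 6 days, giving 11 v 4 looks. That widens the gap, but partly through a real difference in time at risk.
- **Dressing changes are not the only occasion.** Table 2 also marks infection at admission, equally in both arms. Suspicion can arise between changes: fever is visible without opening a dressing, and pain is recorded twice daily. The Flaminal exception, "If an infection is suspected, or in case of leaking or insufficient gel", can add looks. However, looks triggered by suspicion come after the suspicion and do not restore the missed routine ones.
- **A reverse bias might be inferred.** In a day-by-day comparison, Flaminal wounds opened off schedule would be a selected group. The article plans no such comparison, so this is not a fault of the plan.
- **There are partial safeguards.** Colonization swabs are taken on fixed weekdays in both arms, and systemic antibiotic use is a separate outcome. Neither corrects the infection count. The fixed swab days do show that a common assessment calendar was workable.

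**Conclusion.** The point holds in a limited form. The 14 v 8 count follows from the documents. At equal true risk, the direction (more patients called infected with Flamazine, counted per patient) holds whenever false signs are less than fully persistent. It is a tendency in expectation, not a certain result in this trial.

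The size rests on a per-look error rate and a sign duration that the documents do not give. At p = 1–3% the gap by day 14 runs from about 5–13 percentage points with independent looks, through about 2–4 points with signs lasting some two days, to under half a point when signs are long-lasting. True infections that persist are found at most about a day later with Flaminal, so the distortion comes from transient or doubtful signs. The primary endpoint is not at issue here. The point merits a change because infection is a named outcome and the remedy is cheap.

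**What to change.** Add to the definition of the infection outcome, before infection is compared by arm: for the main comparison, count in both arms only judgments made on post-burn days when both regimens have a scheduled dressing change (days 1, 2, 3, 5, 7, 9 and so on). An infection first suspected on any other day counts if it is still judged present at the next common day. Make no separate exception for treatment started: it would let off-day calls back in, mainly from the arm inspected daily. Report all judgments as recorded, including treated off-day infections, as a supportive analysis.

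Every scheduled Flaminal day is also a scheduled Flamazine day, so the rule equalizes scheduled looks by construction for wounds still open and on schedule. It does not remove differences in time at risk or the effect of open-label judgment.

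The cost is a short addition to the outcome definition and a date filter on judgments already being recorded, so it remains feasible with recruitment complete. Care and dressing schedules do not change. The downside is that short-lived or quickly treated off-day infections leave the main count; the supportive analysis shows how many.
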